## Abstract

**Background:**

Amyotrophic lateral sclerosis (ALS) is a fatal neurodegenerative disease that causes paralysis of limb, swallowing, and breathing muscles. Riluzole, the Food and Drug Administration-approved drug for ALS, provides minimal benefit, prolonging patient life by only 2–3 months. Previous studies have found a neuro-protective and anti-neuroinflammatory effect of Mecasin, with retrospective studies providing suggestive evidence for a beneficial effect of Mecasin. The aim of this study was to develop a protocol to determine the proper dosage of Mecasin.

**Methods:**

This is a phase II-A, multi-center, randomized study with three arms. Thirty-six patients with ALS will be randomly assigned to one of three groups, each receiving the standard treatment with 100 mg of riluzole in addition to one of 1.6 g of Mecasin, 2.4 g of Mecasin, or a placebo. The Primary outcome is the Korean version of the Amyotrophic Lateral Sclerosis Functional Rating Scale-Revised result after 12 weeks of treatment. Secondary outcomes include results of the Short Form Health Survey-8, Medical Research Council Scale, Visual Analogue Scale for Pain, Hamilton Rating Scale for Depression, Fatigue Severity Scale, Patient Global Impression of Change, pulmonary function test, forced expiratory volume in 1 s and its ratio to forced vital capacity, creatine kinase, and body weight. The frequencies of total adverse events and serious adverse events will be described and documented. The trial protocol has been approved by the Institutional Review Board of the Wonkwang University Gwangju and Sanbon Hospital (2016–5-4 and 2016–34-01, respectively). An Investigational New Drug status (30731) was granted by the Korea Food and Drug Administration.

**Discussion:**

This trial will aim to identify the optimal dosage of Mecasin. Additionally, it will test the efficacy and safety of Mecasin in conjunction with standard treatment, riluzole, for alleviating the functional decline in patients with ALS.

**Trial registration:**

Korean National Clinical Trial Registry CRIS; KCT0001984. Registered on 28 July 2016.

**Electronic supplementary material:**

The online version of this article (10.1186/s13063-018-2557-z) contains supplementary material, which is available to authorized users.

## Background

Amyotrophic lateral sclerosis (ALS) is a lethal neurodegenerative disorder characterized by focal weakness of the limbs or bulbar muscles, and progressing to involve all skeletal muscles and the loss of both upper and lower motor neurons [1]. Symptoms may rapidly progress over the course of as little as 2–4 years, although some patients may live for up to 10 or more years [2, 3]. Once paralysis of the respiratory muscles occurs, the patient can no longer survive without permanent ventilatory support.

Although various drugs are currently being developed to treat ALS, no drug with a definitive therapeutic effect is yet available. The current status of treatment for ALS includes riluzole and edaravone, which slow ALS progression, and nuedexta, which that reduces emotional outburst; however, none of these drugs is able to completely extend survival, but rather induce a slowing down of patient symptom deterioration [4].

Due to the unremarkable effects of conventional medical treatments, various complementary and alternative therapies are currently used in clinical settings [5]. We have previously prescribed the herbal drug*,* modified *jakyakgamchobuja-tang* to patients with ALS. A retrospective study showed that 3 months of combined therapy consisting of the herbal drug, acupuncture, pharmacopuncture, and needle-embedding therapy alleviated ALS progression. The Korean version of the Amyotrophic Lateral Sclerosis Functional Rating Scale-Revised (K-ALSFRS-R) score increased from 28.42 ± 7.83 to 29.08 ± 7.99 after 1 month of treatment, and decreased to 28.16 ± 8.23 after 3 months. However, it severely decreased to 21.33 ± 9.93 at 8 months from discharge [6]. Another study showed that 30 days of the combined therapy led to a K-ALSFRS-R score increase from 28.42 ± 7.83 to 29.08 ± 7.99 [7]. Mecasin, also known as KCHO-1, a herbal extract from modified *jakyakgamchobuja-tang*, has shown neuro-protective and anti-neuroinflammatory effects and safety in both in vitro and in vivo trials [8–14]. The aim of this study was to develop a protocol to assess the optimal dosage of Mecasin, and to test whether Mecasin alleviates the functional decline in patients with ALS. The study will be a phase II-A, randomized, multi-center, blinded, parallel-group trial with three groups. Additionally, it will aim to assess safety issues.

## Methods/Design

### Primary objective

The primary objective is to investigate the optimal dosage of Mecasin.

### Secondary objectives

The secondary objectives are to determine whether Mecasin, combined with standard ALS treatment, significantly slows the rate of functional deterioration in patients with ALS over 12 weeks, compared with standard treatment alone, and to monitor the safety of Mecasin combined with standard ALS treatment over 16 months. We also aimed to determine whether this treatment affects health-related quality of life, depression, muscle strength, pain, fatigue, pulmonary function, creatine kinase, or body weight in patients with ALS over 12 months.

### Design and setting

This will be a phase II-A, multi-center, randomized, double-blind, placebo-controlled trial. All patients will have taken riluzole for more than 3 months before screening and will be committed to take riluzole during trials. The trial will be conducted at South Korea Wonkwang University Gwangju Hospital and Sanbon Hospital. The flow diagram of the trial is shown in Fig. 1. We will test the effects of 1.6 g and 2.4 g of Mecasin to investigate optimal dosage and treatment efficacy. The schedule of study procedures is depicted in Fig. 2 and details are provided in Table 1.

**Fig. 1 Fig1:**
[figure not shown]
Flow diagram of the study participants. *Follow-up evaluations for adverse events will be conducted by a Clinical Research Coordinator

**Fig. 2 Fig2:**
[figure not shown]
The SPIRIT trial schedule of enrolment, intervention, and assessment. *K-ALSFRS-R* Amyotrophic Lateral Sclerosis Functional Rating Scale-Revised, *SF-8* Short Form Health Survey 8, *MRC* Medical Research Council scale for muscle strength, *mMRC* Modified Medical Research Council Scale for Dyspnoea, *VAS* Pain Visual Analogue Scale for Pain, *HRSD* Hamilton Rating Scale for Depression, *FSS* Fatigue Severity Scale, *PGIC* Patient Global Impression of Change

**Table 1 Tab1:** Schedule of study procedures

	Screening	Treatment and evaluation				
		Baseline			Final	
Visit	Visit 1	Visit 2	Visit 3	Visit 4	Visit 5	Follow-up
Schedule	Week −4 to Day 0	Week 0	Week 4	Week 8	Week 12	Week 16
Informed consent	✓					
Demographic characteristics	✓					
Medical history	✓					
Inclusion/Exclusion criteria	✓					
Chest x-ray	✓					
Pregnancy test	✓				✓	
Electrocardiogram	✓				✓	
Randomization		✓				
Medications	✓	✓	✓	✓	✓	
Vital sign	✓	✓	✓	✓	✓	
Body weight	✓	✓	✓	✓	✓	
Pulmonary function test (FEV_1_/FVC)	✓	✓	✓	✓	✓	
Blood tests^a^	✓	✓	✓	✓	✓	
K-ALSFRS-R	✓	✓	✓	✓	✓	
Short Form Health Survey 8		✓	✓	✓	✓	
Medical Research Council Scale for muscle strength		✓	✓	✓	✓	
Visual Analogue Scale for Pain		✓	✓	✓	✓	
Measurement of Muscular Atrophy		✓	✓	✓	✓	
Hamilton Rating Scale for Depression		✓	✓	✓	✓	
Fatigue Severity Scale		✓	✓	✓	✓	
O_2_ saturation and CO_2_ pressure test		✓	✓	✓	✓	
Provision/collection of test medication and placebo		✓	✓	✓	✓	
Adverse events assessment			✓	✓	✓	✓
Patient Global Impression of Change					✓	

^a^Blood (5 mL) will be collected from each patient to measure creatine kinase and other markers

*K-ALSFRS-R* Amyotrophic Lateral Sclerosis Functional Rating Scale-Revised

### Participants

#### Inclusion criteria

The inclusion criteria are (1) men and women between the ages of 20 and 80 years; (2) a diagnosis of ‘laboratory supported probable’ , ‘probable’ or ‘definite’ ALS according to the revised El Escorial criteria [15]; (3) an K-ALSFRS-R score greater than 20; (4) treatment with 100 mg of riluzole up to 3 months prior to screening; (5) the ability to visit the hospital alone or with the assistance of a caregiver; and (6) the ability to provide voluntary written informed consent.

#### Exclusion criteria

The exclusion criteria are (1) patients with ≤ 30% forced vital capacity; (2) patients with other neurological diseases, including fronto-temporal dementia with communication difficulties and Parkinson’s disease; (3) patients with cardiovascular disease, including ischemic heart disease; (4) patients with hepatic diseases such as hepatic cirrhosis, hepatic cancer and active hepatitis, or aspartate transaminase/alanine transaminase greater than three times the upper normal limit; (5) patients with cholecystitis or biliary obstruction; (6) patients with renal failure or undergoing renal dialysis; (7) patients who have had liver or kidney transplants; (8) patients with interstitial lung disease, as observed on a chest x-ray; (9) patients who have experienced post-operative complications; (10) patients with a history of hypersensitivity to any component of the experimental medications or a similar medication class; (11) patients with genetic disorders (Kennedy’s disease, spinal muscular atrophy type 4) or diagnosis of motor neuron disease due to heavy metal poisoning; (12) patients who have received other experimental medications/procedures within 4 weeks of participating in this trial; (13) pregnant women, lactating women, and women of childbearing age who plan on becoming pregnant (i.e., no history of hysterectomy, bilateral tubal ligation, or bilateral oophorectomy within 2 years of menopause) and who do not agree to use medically appropriate contraceptives (e.g., oral medication, hormone implants, intrauterine devices, condoms, or spermicides), or men who do not agree to use appropriate contraceptives with female partners; (14) patients with primary lateral sclerosis and experiencing only upper motor neuron symptoms or with progressive muscular atrophy and experiencing only lower motor neuron symptoms; (15) patients with bleeding diathesis; (16) patients with malignant tumors; (17) patients who have undergone mechanical ventilation or tracheostomy and percutaneous endoscopic gastrostomy; (18) patients with active viral infections (hepatitis B virus antigen, hepatitis C virus antibody, human immunodeficiency virus antibody, cytomegalovirus immunoglobulin M, Epstein–Barr virus immunoglobulin M, herpes simplex virus type 2 immunoglobulin M, syphilis); (19) patients with a conduction block, including chronic inflammatory demyelinating polyneuropathy and multiple sclerosis; and (20) patients deemed by a clinical research investigator to be inappropriate for participation in the clinical trial.

#### Participant recruitment

The present study aims to recruit 36 participants; all participants will provide written informed consent prior to participation in the study. The participants will be recruited via an advertisement flier and the Internet.

#### Criteria for discontinuing the allocated interventions

The withdrawal criteria are (1) withdrawal of consent by patients or their agents; (2) use of the medication no longer possible due to adverse events or abnormal findings on laboratory tests; (3) an overall compliance rate of less than 80% during the medication period; (4) a violation of the inclusion/exclusion criteria confirmed during the clinical trial; (5) use of combination medication unavoidable; (6) impossible follow-up; and (7) judgment that the trial is difficult to continue by any investigator.

### Sample size

The primary purpose of this trial is to investigate the appropriate dosage for Mecasin, and to examine the efficacy and safety of Mecasin combined with the standard treatment, riluzole. Considering a dropout rate of 20%, 12 participants will be assigned to each of the three groups.

### Randomization, allocation concealment, and blinding

The randomization codes will be generated by an independent statistician with the ratio of Mecasin 1.6 g/day, Mecasin 2.4 g/day, and placebo treatments as 1:1:1 using SAS (Version 9.3, SAS institute. Inc., Cary, NC, USA). The code will be written on a piece of paper, put in a sealed envelope, and stored in a double-locked cabinet. After eligible participants have signed an informed consent form, a researcher who is not involved in recruitment or assessment will open the envelopes and assign the randomization codes. The opened envelope will be stored separately in a double-locked cabinet. Mecasin and placebo will be manufactured as identical-looking tablets. The tablets will be packaged and labelled by a manufacturer who is not involved in participant recruitment, assessment, or assignment. Allocation concealment will be maintained throughout the trial.

### Intervention

#### Mecasin

Mecasin, also known as KCHO-1, contains 30% ethanol extracts of nine medicinal herbs, including *Curcuma longa*, *Salvia miltiorrhiza*, *Gastrodia elata*, *Chaenomeles sinensis*, *Polygala tenuifolia*, *Paeonia lactiflora*, *Glycyrrhiza uralensis*, *Atractylodes lancea*, and processed *Aconitum carmichaeli*. Mecasin will be manufactured by Hanpoong Pharm and Foods Co. (Chonju, South Korea) using certified Good Manufacturing Practices by the Ministry of Food and Drug Safety, and produced as a rectangular maroon tablet with a film coating.

Results of single toxicity tests have revealed a no-observed-adverse-effect level at > 5000 mg/kg/day, while animal studies have reported efficacy at doses of between 250 and 500 mg/kg/day [10, 11]. When the optimum dose is set based on this range, the effective dose for a 60-kg adult is between 15 and 30 g/day, with safe doses up to 120 g/day. The safe dose for this trial has been calculated as 5000 mg/kg × (6/37) × (1/10) × 60 kg = 4.8625 g, while the effective dose has been calculated as 250–500 mg/kg × (3/37) × 60 kg = 1.216–2.432 g. Dosages for each group were determined by selecting a safe dose of 1.6 g (low-dose group) and a safe/effective dose of 2.4 g (middle-dose group).

#### Placebo

The placebo will be a rectangular maroon tablet with a film coating manufactured by the same pharmaceutical company that will manufacture Mecasin. The pharmaceutical ingredients of the placebo tablet will include microcrystalline cellulose, corn starch, light anhydrous silicic acid, carboxymethylcellulose calcium, caramel color, magnesium stearate, a coating substance (hypromellose 2910, polyethylene glycol 6000), and a color additive (black iron oxide, red iron oxide).

#### Riluzole

Riluzole (2-amino-6-trifluoromethoxybenzothiazole, Rilutek®) is currently the standard treatment of ALS. All participants will take riluzole at 100 mg/day.

### Primary outcome

The primary outcome is the difference in the total score on the K-ALSFRS-R from baseline to the last evaluation after the 12th week of treatment. The K-ALSFRS-R [16] is a reliable and useful scale for the evaluation of functional status in patients with ALS. The scale contains 12 questions to assess gross motor tasks, fine motor tasks, bulbar function, and breathing function [17]. A blinded trained researcher will assess the scale. If possible, the same researcher will perform the evaluation at all patient visits.

### Secondary outcomes

The secondary outcomes are the degree of variation of scores at baseline to the last evaluation at the 12th week of treatment of the following measures: the Short Form Health Survey 8 (SF-8), Medical Research Council (MRC) scale for muscle strength, Visual Analogue Scale for Pain (VAS Pain), measurement of muscular atrophy, Hamilton Rating Scale for Depression (HRSD), Fatigue Severity Scale (FSS), Patient Global Impression of Change (PGIC), pulmonary function test, creatine kinase, and body weight.

#### SF-8

The SF-8, a brief version of the widely used SF-36, is a health investigation questionnaire consisting of eight questions that will be administered by a clinical coordinator to assess patients’ physical and mental quality of life, an important dimension when caring for people with ALS [17].

#### MRC and modified MRC (mMRC) for Dyspnea scale

The MRC scale is a five-grade scale used to evaluate muscle strength of both upper and lower extremities [17], and the mMRC for Dyspnea scale is a four-grade scale to evaluate the effects of breathlessness on mobility [18].

#### VAS Pain

As more than 70% of patients with ALS complain of physical pain [19], the VAS Pain is a self-rated scale that will be used to provide a more objective description of the subjective pain experienced in the head and neck, shoulders, upper radicular group, lower back, and lower extremities.

#### Measurement of muscular atrophy

Upper extremity muscle loss will be assessed by measuring the circumference of the arm at the midpoint between the tip of olecranon process and the tip of acromion process. Lower extremity muscle loss will be assessed by measuring the circumference at 15 cm above the upper edge of the bilateral patella [20, 21].

#### HRSD

As patients with ALS complain of depression as the disease progresses [22], the HRSD will be used to evaluate the severity of depression symptoms. The questionnaire consists of 68 items divided into four categories of 17 items each.

#### FSS

Fatigue is a common symptom in ALS [23]. The FSS is used to evaluate fatigue in patients with ALS and consists of nine items, each graded on a 7-point scale.

#### PGIC

The PGIC is a self-reported questionnaire used to evaluate the severity of symptoms, therapeutic responses, and changes in the therapeutic effects during treatment. Patients evaluate overall improvement in symptoms on a 7-point scale [24].

#### Pulmonary function test, creatine kinase, and body weight

ALS is a motor neuron disease resulting in the loss of muscular strength and eventual paralysis of the respiratory muscles. We will measure pulmonary function using spirometry (Spirolab III, Medical International Research), forced expiratory volume in 1 s, and its ratio to forced vital capacity. To evaluate the increase in the levels of creatine kinase due to muscle damage [25], creatine kinase measurement will be included in blood tests. As progression of muscular atrophy could affect body weight, body weight will also be measured.

### Statistical analysis

#### Primary analysis

The population used in the analyses will be the intention-to-treat population. Analyses of covariance (ANCOVA) will be performed to evaluate differences in K-ALSFRS-R scores among the groups at week 12 compared to baseline. The covariates for the ANCOVA will include age, sex, K-ALSFRS-R score, pulmonary function test score, creatine phosphokinase level, body weight, muscle circumference, bulbar onset, and the survey scores used in the secondary outcomes. Moreover, differences before and after treatment within each treatment group will be tested and compared using paired *t*-tests or Wilcoxon signed-rank tests. A repeated-measures analysis of variance will be performed to evaluate changes per visit in each group.

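### The primary ANCOVA is committed to at least 12 covariates on 36 patients, and its wording admits PGIC, which is measured only at week 12 and has no baseline

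*Protocol article*

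**What the plan says.** The Primary analysis section fixes the ANCOVA covariates in one sentence. It names age, sex, K-ALSFRS-R, pulmonary function, creatine phosphokinase and body weight, and then "muscle circumference, bulbar onset, and the survey scores used in the secondary outcomes". It gives no selection rule, no cap and no statement that the values are baseline values. The same section says "The population used in the analyses will be the intention-to-treat population".

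On size, Participant recruitment says "The present study aims to recruit 36 participants", and Sample size says "Considering a dropout rate of 20%, 12 participants will be assigned to each of the three groups". No effect size, standard deviation, alpha or power is given.

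On PGIC, the list of secondary outcomes, all defined as variation from baseline to week 12, ends with "Patient Global Impression of Change (PGIC), pulmonary function test, creatine kinase, and body weight". The PGIC section describes it as a self-reported questionnaire covering response to treatment. In Table 1 the row "Patient Global Impression of Change" has a single tick, at Visit 5 (week 12). The Secondary analysis section applies an ANCOVA of change, paired t-tests against baseline and a per-visit repeated-measures ANOVA to the secondary outcomes, with no exception for PGIC.

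**The concern.** Two separate problems arise from the covariate sentence, and a third from the same gap in the PGIC schedule.

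- **Precision.** In a small trial each covariate costs an error degree of freedom. It also inflates the variance of the treatment contrast through chance imbalance, unless it explains enough outcome variance to pay for itself. A dozen or more covariates on 36 patients can make the primary comparison less precise than a simple model on the same data.
- **Validity.** PGIC is a survey and a listed secondary outcome, so read literally it is a covariate. Its only value is taken at week 12, after treatment, and it measures response. Adjusting for it would condition on a consequence of treatment.
- **Computability.** Without a baseline or repeated PGIC values, the analyses planned for it as a secondary outcome have no data to work on.

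**Working it through.** **Inputs from the protocol.** Three arms, 12 per arm, so N = 3 × 12 = 36. Dropout is 20%, so 36 × 0.8 = 28.8, about 29 completers. There is no power calculation to reproduce.

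**Covariate count.**
- Named singly: age, sex, K-ALSFRS-R, pulmonary function, creatine phosphokinase, body weight, muscle circumference, bulbar onset = 8.
- Survey scores with a baseline value: SF-8, VAS Pain, HRSD, FSS = 4. Total 12.
- Adding either PGIC or the MRC scale gives 13; adding both gives 14.

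**Error degrees of freedom** = N − 3 − k. At N = 36: 21 (k = 12), 20 (k = 13), 19 (k = 14). At N = 29: 14, 13, 12.

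**Precision.** With k non-prognostic baseline covariates, taken as normal, the expected variance inflation of an arm contrast is (N − 4)/(N − 4 − k). The confidence-interval ratio against a three-covariate model is √(inflation ratio) × ratio of two-sided 5% t critical values. The share of residual variance that the extra covariates must explain to break even is 1 − 1/ratio².

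Reference model, k = 3:
- N = 36: inflation 32/29 = 1.103, 30 df, t = 2.042.
- N = 29: inflation 25/22 = 1.136, 23 df, t = 2.069.

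| N | k | Inflation | t | CI ratio vs k = 3 | Break-even share |
|---|---|---|---|---|---|
| 36 | 12 | 32/20 = 1.600 | 2.080 | 1.204 × 1.018 = 1.23 | 33% |
| 36 | 13 | 32/19 = 1.684 | 2.086 | 1.235 × 1.021 = 1.26 | 37% |
| 36 | 14 | 32/18 = 1.778 | 2.093 | 1.269 × 1.025 = 1.30 | 41% |
| 29 | 12 | 25/13 = 1.923 | 2.145 | 1.301 × 1.037 = 1.35 | 45% |
| 29 | 13 | 25/12 = 2.083 | 2.160 | 1.354 × 1.044 = 1.41 | 50% |
| 29 | 14 | 25/11 = 2.273 | 2.179 | 1.414 × 1.053 = 1.49 | 55% |

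These ratios need no assumed effect size. They treat every covariate as a baseline variable. If one of them is PGIC, the formula is only a guide, because PGIC would be related to the outcome and to treatment.

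**PGIC as a covariate.** Suppose the drug affects PGIC only through the K-ALSFRS-R change, with within-arm correlation r between the two. Adjustment then leaves a share 1 − r² of the effect. The protocol does not give r, so a range is shown. The simulation used 12 per arm, one baseline covariate and an assumed true difference of 1.2 SD:

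| r | 1 − r² | Simulated estimate (true value 1.2) |
|---|---|---|
| 0.3 | 0.91 | 1.10 |
| 0.5 | 0.75 | 0.90 |
| 0.7 | 0.51 | 0.62 |

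**PGIC as an outcome.** The Secondary outcomes and Secondary analysis sections require a baseline value and values at several visits. Table 1 supplies one value, at week 12. The two cannot both stand.

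**The case against.** The best defence is that baseline scores were meant. K-ALSFRS-R is in the same list and can only be the baseline value, since its 12-week change is the outcome. On that reading PGIC, having no baseline, drops out and nothing is adjusted away; extra baseline covariates cost precision but do not bias a randomised comparison. This is a fair reading, and it is why 12 is taken as the minimum. But the sentence does not say it, and 12 covariates on 36 patients remain.

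A second defence is that the covariates may be prognostic. That would offset part of the loss, and the zero-prognosis figures are the unfavourable end. The break-even column shows how much the extra covariates would have to explain.

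A third is that PGIC is itself a rating of change, so one assessment is natural. That is true of the instrument, but the planned paired and per-visit analyses still cannot be run on it.

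Several stronger readings are tempting and not supported:
- A reader might count about 22 covariates by splitting pulmonary function, circumference, SF-8, MRC and five pain regions. The covariate sentence names pulmonary function and circumference in the singular, and nothing says the pain regions enter as separate scores.
- A reader might infer that one missing questionnaire removes a patient from the model. The plan specifies intention-to-treat, and missing-data handling may lie in an analysis plan not shown. The N = 29 rows therefore assume complete-case analysis.
- A reader might conclude that PGIC adjustment must shrink the effect. PGIC covers overall symptoms, so effects on other symptoms or tolerability could change the size, or even the sign, of the bias.

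**Conclusion.** The point holds in a limited form. The protocol itself fixes a covariate list that is too long for 36 patients: at least 12, leaving 19 to 21 error degrees of freedom. Against a three-covariate model the expected interval is about 23% wider with 12 covariates and 26% wider with 13, provided that the extra covariates are non-prognostic. They must explain roughly a third of the residual variance to break even. The loss is larger (35% and 41%) if only about 29 patients are analysed. This is a substantial loss of precision, not a collapse of the analysis.

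The bias from PGIC is possible rather than established. It arises only if the sentence is applied literally, and its size rests on an unknown r and on the drug reaching PGIC solely through functional change. That PGIC's change-from-baseline, paired and repeated-measures analyses cannot be computed holds on either reading.

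**What to change.** Before unblinding, reword the covariate sentence along these lines: the primary ANCOVA of the week-12 change in K-ALSFRS-R includes treatment arm, baseline K-ALSFRS-R, bulbar onset and at most one or two further pre-specified baseline covariates, such as age or study hospital. Hospital is optional, since no stratification by site is described. State that all covariates are baseline values and that PGIC is never a covariate. Move the full baseline list to a sensitivity model.

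In the Secondary outcomes and Secondary analysis sections, take PGIC out of the change-from-baseline, paired and repeated-measures analyses. Compare its week-12 score between arms with an ordinal or rank method.

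With three or four covariates, 30 or 29 error degrees of freedom remain at N = 36, with variance inflation of 1.10 to 1.14. The change needs no new data. Its cost is that chance imbalance in a dropped covariate is adjusted only in the sensitivity model.

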#### Secondary analysis

An ANCOVA will be used to compare the changes of secondary outcomes after 12 weeks of treatment among groups. Paired *t*-tests will be used to analyze internal variation of the results obtained at week 12 compared to those obtained at baseline in each group. A repeated-measures analysis of variance will be performed to analyze changes per visit in each group.

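### The primary objective is dose, but no dose contrast is named for efficacy, and the only arm-specific results are within-arm before/after tests to be compared

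*Protocol article*

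**What the plan says.** The Primary objective section states: "The primary objective is to investigate the optimal dosage of Mecasin". The Secondary objectives add whether Mecasin with standard treatment "significantly slows the rate of functional deterioration in patients with ALS over 12 weeks, compared with standard treatment alone". Allocation is "Mecasin 1.6 g/day, Mecasin 2.4 g/day, and placebo treatments as 1:1:1", and the Sample size section says "Considering a dropout rate of 20%, 12 participants will be assigned to each of the three groups".

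For K-ALSFRS-R, the Primary analysis section lists three analyses:

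1. An ANCOVA of week-12 differences from baseline across the groups, with covariates. No reference arm, pairwise contrast or dose trend is named.
2. Within-arm tests: "differences before and after treatment within each treatment group will be tested and compared using paired" t-tests or Wilcoxon signed-rank tests.
3. A repeated-measures ANOVA that "will be performed to evaluate changes per visit in each group". No group or group-by-visit term is mentioned.

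The Secondary analysis section repeats the pattern: ANCOVA across groups, then paired t-tests that "will be used to analyze internal variation of the results obtained at week 12 compared to those obtained at baseline in each group", then repeated-measures ANOVA. The only comparison for which two arms are named is in the Adverse events section, between the two Mecasin groups.

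**The concern.** The question is which dose, and whether either dose beats placebo. The results that attach to a particular arm are before/after tests in that arm, and the text says they will be compared. ALS is progressive, so decline is expected in every arm, including placebo. A significant fall in one arm and a non-significant fall in another is not evidence that the arms differ. With arms of 12, such patterns arise easily by chance.

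At stake is an invalid route to a dose claim. A dose could be described as having halted decline because its paired test missed significance while the placebo test did not. If the repeated-measures ANOVA is run arm by arm, it has the same weakness.

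**Working it through.** The article gives no power calculation for this question, so there is no planned figure to reproduce. The check asks how often the within-arm tests mislead when the drug does nothing.

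**Inputs from the article**
- 12 per arm and 20% dropout (Sample size): 12 × 0.8 = 9.6, taken as 10 completers.
- Post-discharge K-ALSFRS-R fall from 28.16 to 21.33 over 8 months (Background): 6.83 / 8 = 0.854 points per month. Twelve weeks is 12 × 12/52 = 2.77 months, so 0.854 × 2.77 = 2.36 points.
- Change over 3 months on treatment (Background): 28.42 − 28.16 = 0.26 points.

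**Assumed, not in the article:** SD of change of 3, 4 or 5 points; two-sided 5% tests; the same true decline in all three arms; independent arms.

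**Step 1. Chance p that one arm's paired t-test is significant.** This is the power of a one-sample t-test with non-centrality (decline / SD) × √n.

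**Step 2. The misleading pattern.** Placebo is significant and at least one of the two doses is not: p × (1 − p²).

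| Decline | n per arm | SD | p | p(1 − p²) |
|---|---|---|---|---|
| 2.36 | 12 | 3 | 0.70 | 36% |
| 2.36 | 12 | 4 | 0.46 | 36% |
| 2.36 | 12 | 5 | 0.32 | 29% |
| 2.36 | 10 | 3 | 0.60 | 38% |
| 2.36 | 10 | 4 | 0.39 | 33% |
| 2.36 | 10 | 5 | 0.27 | 25% |
| 0.26 | 10 or 12 | 3 to 5 | 0.05 to 0.06 | 5% to 6% |

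Example, n = 12 and SD 3: 0.699 × (1 − 0.699²) = 0.36. At 2.36 points almost every significant result is a decline. At 0.26 points the two-sided test sometimes flags a rise, so the 5% to 6% includes both directions.

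For a single dose named in advance the chance is p(1 − p): 21%, 25% and 22% at n = 12 for SD 3, 4 and 5.

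**Step 3. What a joint test alone would show.** In a simulation (40,000 runs, 12 per arm, SD 4, no covariates), mean changes are listed as placebo, 1.6 g, 2.4 g. The three-arm F test was significant in 43% of runs for (−3, −3, 0), 33% for (−3, −1.5, 0) and 14% for (−3, −1.5, −1.5). A significant F by itself does not say which pattern holds, so the contrasts must be read out.

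**Step 4. What named contrasts would give.** The 95% CI half-width of a pairwise difference is t(0.975; 3n − 3) × SD × √(2/n). At 12 per arm it is 2.5, 3.3 and 4.2 points for SD 3, 4 and 5; at 10 per arm it is 2.8, 3.7 and 4.6. By the normal approximation, 80% power at 12 per arm needs a difference of (1.96 + 0.84) × √(2/12) = 1.14 SD. That is 3.4 points even at SD 3, more than the whole 2.36-point decline.

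**The case against.** The ANCOVA comes first, and it is a baseline-adjusted comparison of the randomised arms. The pairwise dose differences can be taken from that same model, and nothing says it stops at a joint F test. Contrasts and multiplicity rules are commonly left to a statistical analysis plan, which is not at hand. All of this stands. A reader might infer that no planned analysis compares a dose with placebo, or that the dose question cannot be answered. The article does not support that.

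Three further readings also go too far:

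- **A stated decision rule.** No section says a dose will be judged by within-arm p-values. The risk lies in the instruction to compare them under the primary analysis.
- **Separate per-arm ANOVAs that discard dropouts.** The wording allows separate analyses, but also one model with group as a factor. Losing the early visits of about 7 patients (36 × 0.2 = 7.2) assumes complete-case handling. The article does not state that; it names the intention-to-treat population.
- **Disagreement in most trials.** The chance that the three arms disagree in any way, 1 − p³ − (1 − p)³, is 63%, 75% and 65% at n = 12 for SD 3, 4 and 5. That includes patterns which would not favour a dose, so it overstates the relevant risk.

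The decline rate is also open to challenge. It comes from the period after discharge in a retrospective series, and the same series barely changed over 3 months on combined therapy. The lower figure is therefore shown beside it.

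The objection does not remove the text itself. Within-arm tests are written into the primary analysis and are to be compared. An analysis plan that added contrasts would still need to take away their inferential role.

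**Conclusion.** The point holds as a matter of wording. The primary objective is dose, no efficacy contrast involving a dose is named, and the arm-specific results that are named cannot support a claim about drug effect or dose. With no drug effect, the misleading pattern has a chance of about 25% to 38% if patients decline by 2.36 points in 12 weeks, and about 5% to 6% if they decline by 0.26. Both ranges rest on assumed SDs of 3 to 5, equal decline in all arms and 10 to 12 patients per arm. The wording problem does not depend on these figures, because a within-arm test is the wrong comparison at any rate of decline.

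The ANCOVA is sound in kind and can supply the missing contrasts. At this sample size they will be estimates with wide intervals rather than a confirmatory choice of dose, which is a further reason to state them with intervals. The change should be made.

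**What to change.** In the Primary analysis section:

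- Name as the primary results the week-12 adjusted mean differences in K-ALSFRS-R change for 1.6 g versus placebo and 2.4 g versus placebo, with a stated multiplicity adjustment, and the 2.4 g versus 1.6 g difference. Give each with a 95% CI. Take them from the planned ANCOVA or from one model with arm, visit and arm-by-visit terms.
- State that any repeated-measures model includes group and group-by-visit.
- Label the paired tests and any per-arm analyses descriptive, and not a basis for efficacy or dose claims.

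Apply the same to the Secondary analysis section. A mixed model for repeated measures with Dunnett adjustment is one acceptable option, not a requirement; it would need a covariance structure and a small-sample degrees-of-freedom correction.

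The cost is a little more analysis wording and somewhat wider adjusted intervals. With Bonferroni for two contrasts at 12 per arm, the critical value rises from 2.03 to 2.35 on 33 degrees of freedom, about 15% wider. No visit, measurement or treatment changes, since K-ALSFRS-R is already scheduled at weeks 0, 4, 8 and 12 in Table 1.
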